#### fMRI scan

The multimodal fMRI scanning will be performed for patients at T0, T1, and T2, and at T0 for healthy subjects using a Siemens Trio 3 Tesla MRI scanner (Siemens, Erlangen, Germany) in Shanghai Key Magnetic Resonance Laboratory of East China Normal University.① Motor tasks

A block design will be adopted for the task-based fMRI scanning. In each run, there will be five blocks in baseline and five blocks in task state, and each block will last 30 s (as shown in Fig. 3). In addition, each run will be preceded by a 6 s empty scan, thus, the total time for each run will be 5 min and 6 s.

**Fig. 3 Fig3:**
[figure not shown]
Block design for tb-fMRI. Block design for tb-fMRI. A total of 10 blocks include 5 REST and 5 TASK are adopted for the tb-based fMRI. Each block last for 30 s. R, REST; T, TASK

In each task state block, the experimenter will make a passive clench motion of fingers on the subject after receiving the “close” command. Next, the experimenter will make a passive stretching motion of fingers on the subject upon hearing “open”, with a frequency of about 1 Hz and the maximum range. Each subject will be asked to complete two groups of exercise tasks: left-hand passive clenching and right-hand passive clenching. Notably, each subject will receive relevant stimulus task training and guidance prior to fMRI.② Data acquisition

The multimodal scans will be performed in accordance with the parameters listed in Table 3. TE is the time of echo, TR is the time of repetition, MPRAGE is magnetization prepared rapid acquisition with gradient echo sequence, TSE is turbo spin echo sequence, and SS-EPI is single shot gradient echo imaging sequence. In addition, for DTI, the diffusion weighted images will be acquired along 10 diffusion directions with b = 0 and 64 different diffusion directions with b = 1000 s/mm2.

**Table 3 Tab3:** Parameters of multimodal MRI

Modal	TR (ms)	TE (ms)	Flip angle (°)	Number of slices	Slice thickness (mm)	Slice spacing (mm)	Sequence
3D high resolution T1-weighted image	2530	2.98	7	192	1	0.5	MPRAGE
T2-weighted image	6000	95	120	30	5	0	TSE
rs-fMRI	2000	30	90	30	4	0.8	SS-EPI
tb-fMRI	3000	30	90	30	5	0	SS-EPI
DTI	8500	63	90	75	2	0	SS-EPI

### Data processing and analysis

#### MRI preprocessing

MRI data will be preprocessed using SPM 8 software. The data of patients with left hemisphere lesions will be flipped along the midsagittal plane to ensure that all the patients have “virtual” right hemisphere lesions. SPM 8 will also be used for BLOD fMRI data preprocessing. Slicing timing, realignment, normalization, and smoothing will be performed on the BLOD fMRI data. Next, the data with translation parameter greater than ±2.5 mm or rotation parameter greater than ±2.5 degrees will be removed. Finally, the diffusion toolkit software (http://www.trackvis.org/dtk/) will be used to pre-process the DTI data.

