### Inclusion and exclusion criteria

A total of 60 eligible patients will be recruited from Huashan Hospital, Fudan University. The inclusion and exclusion criteria are listed in Table 1.

**Table 1 Tab1:** Inclusion and exclusion criteria

Criteria	Description
Inclusion criteria	➤ First-ever stroke ➤ Subcortical stroke diagnosed by head CT or MRI ➤ Clear consciousness and stable vital signs ➤ 18–80 years old ➤ 3–12 months since stroke onset ➤ Unilateral hemiplegia, Brunnstrom stage of affected hand ≤ IV ➤ Right-handed
Exclusion criteria	➤ Severe speech, attention, hearing, vision, sensation, intelligence, mental, or cognitive impairments (MMSE score < 27) ➤ Severe spasticity (Modified Ashworth Spasticity Scale > 2) or pain (Ten-point Visual Analog Scale > 4) of the affected side ➤ Bone, joint, and muscle diseases, other serious nervous system diseases, malignant tumors, and serious heart, lung, liver, and kidney damage ➤ Still enrolled in any rehabilitation or drug studies ➤ Metal implant, magnetic sheet, or cardiac pacemaker ➤ Alcohol or drug addiction ➤ Epilepsy

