### Randomization and grouping

The 60 eligible stroke patients will be randomly assigned to three groups with 20 patients in each group: low-frequency rTMS of cM1 (cM1-LF) group, high-frequency rTMS of cPMd (cPMd-HF) group, and sham-stimulation control (CON) group. The random sequence will be created using STATA 12.0 software (StataCorp, Texas, USA) by a professional third-party statistician from Fudan University. The randomization list will only be known by this research coordinator and will be concealed from other study personnel. However, the research coordinator will not participate in recruitment, subsequent intervention and assessment, and final data analysis. In addition, 20 healthy people will be recruited into the healthy control (HC) group. The HC group will be matched with stroke groups in terms of age, gender, and education.

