#### Group-level analysis

All statistical analyses will be performed using SPSS software (SPSS 25.0, SPSS Inc., Chicago, Illinois). The intention-to-treat principle will be used for the analysis of functional and electrophysiological data. One-way analysis of variance (ANOVA) will be used to compare the demographic characteristics and baseline assessment (T0) of all outcomes among groups. To compare the treatment effects of different rTMS protocol, a two-way mixed design ANOVA with between-subject factor “Group” and within-subject factor “Time” will be performed for the clinical and electrophysiological changes. Moreover, Bonferroni correction will be employed for post hoc multiple comparisons. *P* < 0.05 will be considered statistically significant for all analyses.

For rs-fMRI and DTI data, a two-way mixed design ANOVA will be performed, with between-subject factor “Group” and within-subject factor “Time” on the data generated in the data processing step, including Eg, El, network betweenness, clustering coefficient, and FA AI. For tb-fMRI data, a whole brain paired T-test will be performed between the task state blocks and baseline blocks in the FC group, and the voxels whose t value is higher than the threshold will be regarded as the activated brain region. For cM1-LF, cPMd-HF, and CON groups, a two-way mixed design ANOVA, with between-subject factor “Group” and within-subject factor “Time” will be performed within the former activated brain region. The most significant point of “Group” × “Time” effect in the activated brain region will be used as the center to construct spherical balls with a radius of 6 mm, and the spherical balls will be regarded as the ROIs. Finally, to obtain the effective connectivity of each patient at different time points, the average time series of all voxels in each ROI will be subjected to dynamic causal model (DCM) analysis.

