#### Correlation analysis

Pearson correlation analysis will be performed between electrophysiological parameters, MRI parameters, and clinical function scores in cM1 LF group and cPMd HF group. The statistical threshold will be set to *p* < 0.05.

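### Left-lesion scans of right-handers are mirrored, but the imaging models and imaging-function correlations have no lesion-side term, so a side or flip difference can enter imaging levels and pooled correlations

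*Protocol article*

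**What the plan says.** All points are in the protocol article.

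- **Eligibility (Table 1).** Patients must be right-handed. The hemiplegia criterion reads "Unilateral hemiplegia, Brunnstrom stage of affected hand ≤ IV", which leaves the affected side open.
- **MRI preprocessing.** "The data of patients with left hemisphere lesions will be flipped along the midsagittal plane", so that every lesion appears on the right.
- **Randomization and grouping.** "The 60 eligible stroke patients will be randomly assigned to three groups with 20 patients in each group". No balancing on lesion side is described.
- **Group-level analysis, imaging.** "For rs-fMRI and DTI data, a two-way mixed design ANOVA will be performed, with between-subject factor “Group” and within-subject factor “Time". The tb-fMRI model for the three patient groups has the same two factors.
- **Group-level analysis, clinical.** "a two-way mixed design ANOVA with between-subject factor “Group” and within-subject factor “Time” will be performed for the clinical and electrophysiological changes".
- **Correlation analysis.** "Pearson correlation analysis will be performed between electrophysiological parameters, MRI parameters, and clinical function scores", run in the two active groups at p < 0.05, with no adjustment named.
- **Discussion.** The joint analysis of imaging and function is meant to give prognostic markers and a cut-off for choosing the stimulation strategy.

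**The concern.** Because every patient is right-handed, lesion side fixes two other things. A left-lesion patient has a paretic dominant hand, and the contralesional hemisphere is the right one. A right-lesion patient is the reverse. Mirroring aligns the lesions but not the normal differences between the hemispheres. After it, one label covers both kinds of hemisphere, and whether a scan was flipped is the same variable as true lesion side.

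The stated imaging models have nothing to absorb such a difference. If an imaging measure and a function score both differ by side, pooling the two kinds of patient within an arm can create, strengthen or mask a correlation. The plan intends to read such correlations as mechanism and to use the joint analysis for markers and a treatment-selection cut-off.

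**Working it through.** The plan gives no figure for this point, so there is none to reproduce. The left:right mix and the size of any side difference are also not given. Ranges are assumed for both.

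**1. How side enters a contralesional-versus-affected measure.** The DTI section defines FA AI = (FAc − FAa)/(FAc + FAa). Let δ = (FA_left − FA_right)/(FA_left + FA_right) be a natural asymmetry unrelated to the stroke.
- Right lesion: c is left, so asymmetry alone gives FA AI = +δ.
- Left lesion: c is right, so asymmetry alone gives FA AI = −δ.

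Before any lesion effect, the two kinds of patient differ by 2δ. This comes from the contralesional/affected labelling, not from a flipping artefact. It applies to any measure read by hemisphere.

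**2. Where it cancels.** A side difference that is constant over T0, T1 and T2 is removed from Group x Time, for imaging and clinical outcomes alike. It stays in the between-subject level, and in any correlation that uses levels. The article does not say whether the correlations use levels or changes. With changes, only a side-dependent change would enter.

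**3. Correlation from pooling alone.** Let a share p have left lesions, let both variables differ by D within-side SDs in the same direction, and let them be unrelated within side. Then r = p(1−p)D² / [1 + p(1−p)D²].

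| D | p = 0.5 | p = 0.3 |
|---|---|---|
| 0.2 | 0.04·0.25/1.01 = 0.01 | 0.01 |
| 0.5 | 0.0625/1.0625 = 0.06 | 0.0525/1.0525 = 0.05 |
| 0.8 | 0.16/1.16 = 0.14 | 0.12 |
| 1.0 | 0.25/1.25 = 0.20 | 0.21/1.21 = 0.17 |

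**4. Against the significance threshold.** For n = 20, t(0.975, 18 df) = 2.101, and the critical |r| = 2.101/√(18 + 2.101²) = 0.444. By simulation at p = 0.5 with 20 patients, the chance of a significant correlation is 5.0% with no side difference, about 5.6% at D = 0.5 and about 13% at D = 1.0.

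**5. The randomised contrast.** Assume p = 0.5 and simple randomisation to 20 per arm. Two given arms differ by at least 4 patients in lesion side with probability 0.268 (two independent Binomial(20, 0.5) counts). Some pair of the three does so with probability about 0.51 (simulation). A 4/20 gap moves a contrast of changes by 0.2 times the side difference in change. At an assumed 0.5 SD that is 0.1 SD, or 1.7 points if the SD of 17 in the sample size section applies.

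Simulated variance of a two-arm contrast, unadjusted over side-adjusted:

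| Side difference in change | Variance ratio |
|---|---|
| 0 | 0.98 |
| 0.25 SD | 1.00 |
| 0.5 SD | 1.04 |
| 1.0 SD | 1.23 |

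Adjustment gains nothing at 0.25 SD or below. Against that SD of 17, a 1.0 SD side difference in change would be 17 points, more than the 13-point rise (30 to 43) used for sample size, so the top of the range is extreme.

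**6. Cost of the term.** With 60 patients the between-subject error falls from 57 to 56 degrees of freedom. A partial correlation at n = 20 has 17 instead of 18, and the critical |r| moves from 0.444 to 0.456.

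**The case against.** The strongest reply is that this is one omitted covariate in a condensed account of a randomised trial. A Group-by-Time model is valid without it, covariates are often left to an analysis plan, and nothing in the article forbids a side term. For the clinical and electrophysiological outcomes this stands. All arms have the coil placed on the contralesional side, so side is unrelated to arm in expectation, and chance imbalance is already reflected in the standard error. It stands less well for imaging, where the plan itself introduces the mirroring and then names the factors of the models that follow.

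Three stronger readings are tempting, and the documents do not support them.

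- A reader might infer that the treatment comparison is biased. It is not. A stable side difference cancels in Group x Time, and no side-dependent change is documented.
- A reader might infer that lesion side is concealed. Mirroring is openly stated, applies to MRI only, and serves to align lesions. Side is known for every patient because it decides who is flipped.
- A reader might infer that the right-handed criterion shows an intent to hold dominance fixed. Table 1 gives no reason for it.

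It is also fair to say that correlations of 0.06 to 0.20 would seldom be significant alone. What remains is that they add to, or subtract from, whatever true correlation exists.

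**Conclusion.** The point holds for imaging levels and for the imaging-function correlations, as an inexpensive improvement and not as a flaw that threatens the trial. With both variables differing by an assumed 0.5 to 1.0 SD between sides and an even split, pooling alone contributes r of about 0.06 to 0.20. The chance of a spurious significant correlation at n = 20 rises from 5% to about 6% to 13%. At 0.2 SD the contribution is negligible (0.01). For the clinical Group x Time test there is no bias. The only possible loss is precision or chance imbalance from a side-dependent change whose size is unknown. All magnitudes rest on the assumed side mix and side differences.

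**What to change.** - Keep true lesion side (left or right, before mirroring) as a variable in the analysis data set.
- In Group-level analysis, add lesion side and Side x Time as nuisance terms to the rs-fMRI, DTI and tb-fMRI group models.
- In Correlation analysis, replace plain Pearson correlations that involve MRI parameters with partial correlations adjusted for lesion side, and state whether levels or changes are correlated.
- Optionally, prespecify a sensitivity analysis of the clinical and electrophysiological models with the same terms. The main clinical model need not change.

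The choice should be fixed before unblinding, so that it is not data-driven. These terms remove a side difference common to the arms. They do not test whether side modifies the effect of stimulation. That would need Side x Group x Time, with about 10 patients per cell at an even split, and is not proposed.

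The cost is analysis wording and one or two degrees of freedom, about 2% precision if side has no effect. Enrolment, randomisation and treatment are unchanged.

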#### Rs-fMRI

A total of 90 network nodes will be defined according to Anatomical Automatic Labeling (AAL) atlas. Pearson correlation analyses will then be performed on the preprocessed RS fMRI data, which will result in one 90 × 90 correlation matrix representing the functional connection between each two network nodes. A threshold will be used to binarize the matrix, and all correlation coefficients greater than the threshold will be assigned 1, otherwise 0. Topology attributes, including global network efficiency (Eg), local network efficiency (El), network betweenness, and clustering coefficient will be calculated for each patient based on the correlation matrix.

#### Tb-fMRI

For each patient, the preprocessed task fMRI data will be used to construct a general linear model (GLM) according to the experimental design, with a regression on the head-motion parameters.

#### DTI

The bilateral posterior limb of internal capsule (PLIC), bilateral cerebral peduncle, and corpus callosum of each patient will be delineated manually by two radiologists. For each patient, the common part of the results recorded by the two radiologists will be adopted as the regions of interest (ROIs). The mean fractional anisotropy (FA) will be calculated with all the ROIs for each hemisphere. Notably, FA asymmetery index (FA AI) is defined by the following formula:

$$FA\ AI=\frac{\left({FA}_c-{FA}_a\right)}{\left({FA}_c+{FA}_a\right)}$$where FAc is the FA of the contralesional hemisphere and FAa is the FA of the affected hemisphere. FA AI can be used to quantitatively evaluate the structural integrity of CST and corpus callosum.

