The interhemispheric inhibition (IHI) model, which is commonly used as the fundamental theory for standardized rTMS treatment, was first proposed by Murase in 2004 [22], which suggests that the bilateral primary motor cortexes (M1) are connected through the corpus callosum in a balance of competing inhibition in healthy individuals. However, the IHI balance is disturbed after the onset of stroke, thereby leading to over activation of the contralesional hemisphere. Specifically, damage to the affect hemisphere weakens its inhibitory effect on the contralesional hemisphere, ultimately resulting in abnormally increased excitability of cM1. Notably, the over activation of cM1 will in turn inhibit the affect M1, causing a vicious circle. The disrupted balance between bilateral M1 will eventually hinder the motor output and impede the recovery of upper limb motor function in stroke survivors. Ideally, according to the standardized treatment protocol [19, 20], high-frequency rTMS is able to increase the excitability of affected M1, whereas low-frequency rTMS is capable of reducing the excitability of cM1, thereby enabling the disrupted IHI to reach a new equilibrium. However, some studies have found that the standardized rTMS protocol is not suitable for all stroke patients [11, 12]. It is worth noting that patients with severe hemiplegia seem to be less suitable for this standardized rTMS protocol [19]. This has led to some researchers questioning the value of classic IHI imbalance theory in clinical practice. Pino et al. [23] proposed the bimodal balance-recovery model in stroke recovery, which suggests that determining the mode of recovery to be adopted depends on the degree of damage to the affected hemisphere, namely structural reserve. For example, in patients with less damage (higher structural reserve), the classic IHI imbalance mode will dominate the recovery process, and the increased activation of contralesional hemisphere will not be conducive to motor recovery. In such cases, standardized low frequency rTMS of cM1 can exert therapeutic effects by inhibiting this abnormal excitability. In contrast, for patients with low structure reverse, the recovery process will be dominated by the compensatory mode because the increased motor cortex excitability on the unaffected side will be conducive to rehabilitation. In this case, the standardized low-frequency rTMS protocol might not be effective, and thus applying high-frequency rTMS on cM1 is a better option. Taking these two recovery models together, we believe that if we can identify the cut-off of structural reserve, we might be able to evaluate the real effects (inhibitory or compensatory) of the contralesional hemisphere on motor output. This will aid in selecting the optimum rTMS stimulation strategy on contralesional hemisphere (low frequency or high frequency).

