### Aims and hypotheses

This study will conduct a longitudinal, single-blinded, randomized controlled trial to verify the clinical effects of different protocols of rTMS therapy on functional recovery of chronic subcortical stroke patients with severe hemiplegic upper limb. To the best of our knowledge, this is the first study to compare the effects of low-frequency rTMS on cM1 and high-frequency rTMS on cPMd. We expect that the findings will provide vital information about the optimal rTMS strategy. Multimodal fMRI scanning and electrophysiological measurements will be performed longitudinally to elucidate the underlying neural mechanism of brain reorganization after different parameters of rTMS therapy. We hypothesize that high-frequency rTMS on cPMd might be the optimal protocol for motor functional recovery in chronic subcortical stroke patients with severe hemiplegia. This clinical effect may be attributed to the specific remodeling patterns of structural, functional, or effective connectivity of homologous or allogeneic cortexes within or between hemispheres through multimodal neural imaging analysis. Furthermore, joint analysis of the clinical and neuroimaging results might identify the cut-off of structural reserve that determines the application of high/low frequency rTMS on contralesional hemisphere to achieve maximum functional recovery of the paretic upper limb.

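### The FA asymmetry index cannot measure corpus callosum integrity as claimed, and if the callosum is pooled into the hemispheric means it also shrinks the corticospinal signal

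*Protocol article*

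**What the plan says.** The DTI section of the protocol article names the regions: "The bilateral posterior limb of internal capsule (PLIC), bilateral cerebral peduncle, and corpus callosum of each patient will be delineated manually by two radiologists". The internal capsule and peduncle are called bilateral. The callosum is not, and no rule is given for dividing it between the sides. The section then says "The mean fractional anisotropy (FA) will be calculated with all the ROIs for each hemisphere" and defines FA AI = (FAc − FAa)/(FAc + FAa), "where FAc is the FA of the contralesional hemisphere and FAa is the FA of the affected hemisphere". It concludes that "FA AI can be used to quantitatively evaluate the structural integrity of CST and corpus callosum".

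The Group-level analysis section takes imaging variables into a Group × Time mixed ANOVA, "including Eg, El, network betweenness, clustering coefficient, and FA AI". FA AI is the only DTI variable named there. Elsewhere, Background equates the quantity that decides the mode of recovery with "the degree of damage to the affected hemisphere, namely structural reserve", and Aims and hypotheses expects that "joint analysis of the clinical and neuroimaging results might identify the cut-off of structural reserve".

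**The concern.** An asymmetry index measures a difference between sides. That suits paired tracts such as the internal capsule and the peduncle. The callosum is a commissure crossing the midline, so what matters is how intact it is overall, not whether one side differs from the other.

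Two things are at stake.

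- **Callosal change.** Background rests the interhemispheric inhibition model on callosal connections, and argues for the premotor target partly from the share of callosal fibres that link the two premotor cortices. The one DTI variable named for analysis could not show a change common to both sides of that structure.
- **Corticospinal signal.** If callosal FA enters both hemispheric means, the index no longer depends on the corticospinal regions alone. FA AI is a likely basis for the structural-reserve cut-off, and a cut-off on such an index would depend on callosal FA and on how much weight the callosal region happened to have.

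**Working it through.** The protocol states no FA value and no value of the index, so there is no figure to reproduce. The formula is the protocol's. All FA values and weights below are assumptions for illustration.

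**1. Callosum alone.** Let callosal FA be K.
- Undivided region: there is one K, so FAc and FAa are not separately defined.
- Split at the midline with equal halves: AI = (K − K)/(K + K) = 0 for every K. A callosum at 0.70 and one at 0.35 both give 0.

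This holds however the sentence on averaging is read.

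**2. Pooled index.** Let corticospinal FA be C (contralesional) and A (affected), and let callosal FA K carry weight w in both hemispheric means:

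FAc = (1 − w)C + wK, FAa = (1 − w)A + wK

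AI = (1 − w)(C − A) / [(1 − w)(C + A) + 2wK]

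K is absent from the numerator and present in the denominator, so for any w > 0 and C ≠ A the pooled index is nearer to 0 than (C − A)/(C + A).

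With C = 0.60, A = 0.40, K = 0.70:

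| Callosal weight w | FAc | FAa | AI | Loss against 0.200 |
|---|---|---|---|---|
| 0 (corticospinal only) | 0.600 | 0.400 | 0.200 | – |
| 1/3 (three regions, equal weight) | 0.633 | 0.500 | 0.118 | 41% |
| 1/2 | 0.650 | 0.550 | 0.083 | 58% |
| 0.7 | 0.670 | 0.610 | 0.047 | 77% |

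Range over a second set of assumptions (contralesional corticospinal FA 0.65, affected-side loss 10–40%, callosal FA 0.6–0.8): the pooled index keeps 72–81% of the corticospinal-only value at w = 0.2, 57–67% at w = 1/3, and 14–21% at w = 0.8.

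**3. Callosal loss in the pooled index.**
- Corticospinal regions intact: AI = 0 whatever the shared callosal loss.
- Corticospinal loss of 20% (0.65 against 0.52), w = 1/3: callosal FA falling from 0.70 by 0, 10, 20, 30 and 50% gives AI = 0.070, 0.072, 0.075, 0.078 and 0.086.

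Callosal damage therefore moves the index slightly, and in the same direction as more corticospinal damage. The two cannot be separated.

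**4. Region size.** Under voxel averaging, w depends on the relative size of the manual regions, which are cut down to the overlap of two raters and used for scans at T0, T1 and T2. With the FA values of step 2:
- w = 0.45: AI = 0.110/1.180 = 0.093
- w = 0.55: AI = 0.090/1.220 = 0.074

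The index moves with no change in tissue. If region means are averaged with equal weight instead, this variation disappears but the shrinkage remains.

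**The case against.** **Pooling is a reading, not a stated rule.** The sentence could mean one mean per region and hemisphere, with an index for each structure. This stands: the shrinkage would then vanish. Step 1 would not, and the claim about the callosum would still be wrong.

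**The callosal halves may differ.** With a contralesional half at 0.70 and an affected half at 0.63 or 0.56, a callosum-only index is 0.053 or 0.111, and the pooled index at w = 1/2 (corticospinal 0.60/0.40) is 0.116 or 0.150 rather than 0.083. So a split region would register one-sided loss. That is still a measure of asymmetry and not of integrity, because loss common to both halves stays invisible.

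**Shrinkage is mostly a change of scale.** A reader might infer that losing 41–77% of the index weakens its relation to outcome by a similar amount. It does not. At fixed callosal weight and FA the pooled index is almost a linear function of the corticospinal one: in a simulation with corticospinal loss of 10–40%, callosal FA 0.70 and w of 1/3, 1/2 or 0.7, they correlate at 0.999 or more. Harm needs variation in callosal weight or FA between patients or visits. With a standard deviation of w of 0.03 the correlation is 0.95–0.99; at 0.10 it is 0.68–0.89. The protocol gives no basis for choosing between these.

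**FA AI is not declared the reserve measure.** A reader might also infer that it is the only structural-reserve marker in the plan, or that callosal change will certainly be missed. The document does not say so. It never ties the cut-off to FA AI, its list of analysed variables is introduced as non-exhaustive, and the affected-side motor evoked potential status is also recorded.

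**Conclusion.** The protocol credits FA AI with a property it cannot have. That conclusion rests on the formula alone and holds under either reading of the averaging sentence: callosal loss shared by both sides leaves a callosal index at exactly 0.

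The shrinkage is conditional. It needs the pooled reading, which the wording favours, and callosal FA about equal on the two sides. Its direction is then certain. Its size is not: 0.20 falling to 0.083 is one illustration, and the retained share runs from about 14% to 81% over the weights and FA values tried. Shrinkage as such mainly rescales the index. The practical damage comes from callosal FA or region size varying between patients or visits, which would add noise and make a cut-off hard to carry to another dataset.

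The point concerns the mechanistic aim and, probably though not expressly, the structural-reserve cut-off. The randomised comparison of clinical outcomes, and the sample size based on the Fugl-Meyer upper limb score, are unaffected. The change is worth making because FA AI is the only DTI variable named for analysis.

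**What to change.** 1. Compute FA AI from the posterior limb of the internal capsule and the cerebral peduncle only, and state whether it is one value per region or their mean.
2. Analyse corpus callosum mean FA as a separate variable, in the same Group × Time ANOVA for the patient groups and against the healthy controls at T0, the one visit at which they are scanned.
3. Delete the statement that FA AI evaluates the corpus callosum, leaving it as a measure of corticospinal asymmetry.

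The cost is a few changed sentences and one more DTI variable to analyse. The callosal region is already among those planned for delineation and the healthy controls already have an MRI visit, so no new data are needed.
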